
For the secondary outcomes listed above, the measurements are conducted at baseline, in week 8, 16 and 24. Besides, the satisfaction of patients in two groups and the proportion of the subjects who identified their allocation will be measured in week 8.

Additionally, we will assess the patients’ satisfaction in week 24 by two questions. 1) “Would you like to come for more treatments or recommend it to your friends/relatives if they have similar symptoms?” The answer will be either “yes” or “no”. 2) "What is your feeling for the series of treatment?” The answers will include “excellent”, “good”, “satisfactory”, “It’s okay” and “poor”. The difference in satisfaction between two groups will be analyzed.

To evaluate the success rate of blinding, we will ask subjects in week 8 “how deep do you think the needles went into your skin?” The answer will be “deep”, “shallow” or “no penetration”. The subjects in the two groups whose answers are either “deep” or “shallow” will be considered to be blinded successfully, while “no penetration” unsuccessfully, and the proportions of them are going to be compared.

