### Sample size

Sample size will be decided by the primary outcome. According to our unpublished pilot study and literature review [6], the proportions of patients with a more than 30% improvement in NAS scores in at least 2 out of 3 DPF items for acupuncture and placebo is 45% and 17.9% respectively. We use the proportion for placebo instead of the one in sham acupuncture group, because no data are available for sham acupuncture so far. A sample size of 52 for each group will be sufficient to detect a 2% null difference in proportion, with a two-sided 5% level of significance, and a power of 80%. The number of subjects is increased to 60 in each group (total of 120) when a drop-out rate of 15% is taken into consideration.

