### Statistical analysis

For data analysis, statisticians and investigators will be blinded for the patients’ allocation. Statistical analysis will be performed using SPSS Ver.20 (SPSS Inc., Chicago, IL, USA) software. Enumeration data will be described as frequency and composition ratio. Continuous data will be presented by Mean ± Standard Deviation (M ± SD) if they meet normal distribution, otherwise they will be expressed as Medians ± Interquartile Range (M ± IQR). Categorical data will be presented by frequency and percentage. The analyses of efficacy will be based on the intention-to-treat (ITT) analysis set, which was defined as patients who receive at least one treatment. Missing data for the primary outcome will be treated by multiple imputation under chained equation, with m = 50 imputations. The covariates used to generate the multiple imputed data sets are age, sex, NAS scores of DPF, ESSDAI, ESSPRI, salivary flow rate, and Schirmer test score. For comparison with the baseline, a repeated measures data analysis of variance (ANOVA) or Wilcoxon signed rank test will be used for continuous data, whereas Chi-square test or Fisher exact test will be used for categorical data. In terms of comparison between the two groups, Chi-square test or Fisher exact test will be used for primary outcomes. For secondary outcomes, the analysis of covariance (ANCOVA) will be used if the residual are normal distributed, otherwise Wilcoxon rank sum test will be applied. To access the success of blinding, the proportion of subjects who are successfully blinded will be compared by Chi-square test or Fisher exact test. And nonparametric test will be used to analyze satisfaction. *P* <0.05 with two-tailed test indicates statistical significance.

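### The between-arm test for each secondary outcome is chosen from the trial's own residuals, and the fallback rank sum test cannot adjust for the baseline value that is collected

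*Protocol article*

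**What the plan says.** The Statistical analysis section of the protocol article gives one rule for the between-arm comparison of secondary outcomes: "the analysis of covariance (ANCOVA) will be used if the residual are normal distributed, otherwise Wilcoxon rank sum test will be applied". The significance threshold is P "<0.05 with two-tailed test indicates statistical significance". The section does not name the ANCOVA covariate. It also does not say whether the rank sum test would be applied to follow-up values or to changes from baseline.

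The Secondary outcome section shows that a baseline exists: "For the secondary outcomes listed above, the measurements are conducted at baseline, in week 8, 16 and 24". The list includes ESSPRI, ESSDAI, the Schirmer test, unstimulated salivary flow, immunoglobulins, SF-36, salivary gland ultrasound and the HAD scale. The individual NAS items also have a baseline score.

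The Sample size section concerns the primary responder outcome only. No correlation, SD, effect size or power is given for any secondary outcome.

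**The concern.** Three things follow from the rule as written.

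- **The residuals select the method.** They do so outcome by outcome and, with visits at weeks 8, 16 and 24, possibly visit by visit. The same endpoint could be analysed by ANCOVA at one visit and by a rank test at the next.
- **The two branches answer different questions.** ANCOVA estimates an adjusted mean difference. The rank sum test compares the two distributions by rank and gives no adjusted difference. Results that come from different branches cannot be lined up.
- **The fallback cannot take a covariate.** Whatever ANCOVA would have adjusted for is dropped when the switch occurs, although a rank method that adjusts for baseline is available.

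At stake are the power of the secondary comparisons and their consistency across outcomes and visits. False-positive control is not the issue.

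**Working it through.** **1. The plan's own figure.** The only computed figure is the primary-outcome sample size: "A sample size of 52 for each group will be sufficient to detect a 2% null difference in proportion", with response rates "for acupuncture and placebo is 45% and 17.9% respectively". It is reproduced here only to justify 52 per arm below. The mean rate is (0.45 + 0.179)/2 = 0.3145, and the difference less the null value is 0.271 − 0.02 = 0.251.

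n = [1.960·√(2 × 0.3145 × 0.6855) + 0.842·√(0.45 × 0.55 + 0.179 × 0.821)]² / 0.251² = 52.3, in line with the stated 52.

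**2. Normal errors, closed form.** Let ρ be the baseline-to-follow-up correlation (assumed), and let the effect be such that ANCOVA has 80% power (noncentrality 1.960 + 0.842 = 2.802). The rank sum test has relative efficiency 0.955.

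- On follow-up values: power = Φ(2.802·√(0.955(1 − ρ²)) − 1.960)
- On change: power = Φ(2.802·√(0.955(1 + ρ)/2) − 1.960)

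| ρ | Follow-up values | Change |
|---|---|---|
| 0.3 | 74% | 60% |
| 0.5 | 66% | 66% |
| 0.6 | 59% | 69% |
| 0.7 | 50% | 71% |

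These shortfalls from 80% are large, but they belong to data in which the switch should rarely occur. In simulation, a Shapiro test on near-normal data triggered it in 4–7% of data sets. The protocol names no normality test, so that trigger is itself an assumption.

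**3. Skewed data, where the fallback is meant to apply.** Assumptions: gamma with shape 2, 52 per arm, a true shift of 0.5 SD, two-sided 5%. Rank ANCOVA (Quade) ranks baseline and follow-up over both arms, regresses one set of ranks on the other, and compares the residuals between arms. Simulated power (%):

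| ρ | Rank ANCOVA | Rank sum, follow-up | Rank sum, change | Ordinary ANCOVA |
|---|---|---|---|---|
| 0.3 | 88 | 85 | 63 | 75 |
| 0.4 | 88 | 84 | 69 | 75 |
| 0.6 | 95 | 85 | 86 | 87 |
| 0.75 | 98 | 86 | 96 | 95 |

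Differences, in the order of the rows:

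- Rank ANCOVA minus rank sum on follow-up: 3, 4, 10, 12 points.
- Rank ANCOVA minus rank sum on change: 25, 19, 9, 2 points.
- Rank sum on follow-up minus ordinary ANCOVA: +10, +9, −2, −9 points.

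Repeat runs give similar figures. With 3,000 runs at ρ = 0.3/0.4/0.5/0.6/0.75, rank ANCOVA had 88/90/92/95/99%, rank sum on follow-up 85/85/84/83/86%, and rank sum on change 65/70/76/85/97%. The shortfalls are 3/5/8/12/13 and 23/20/16/10/2 points. With 1,500 runs at 0.4/0.6/0.75, rank ANCOVA had 89/96/99% against 85/85/84% for rank sum on follow-up, a shortfall of 4/11/15. Taken together, the shortfall is about 3 to 15 points on follow-up values and about 2 to 24 on change. Type I error was near 5% for all methods.

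**4. Sensitivity to shape and effect.** Other error shapes were tried (t with 3 df, exponential, lognormal, contaminated normal), with the effect set so that ANCOVA would have 80% power under normal errors. The follow-up rank sum test then fell short of rank ANCOVA by about 0.5 to 4 points at ρ = 0.3 and by 30 to 34 at ρ = 0.7. Against ordinary ANCOVA it gained 9 to 17 points at 0.3 and lost 20 to 26 at 0.7. The ordering of the rank methods is stable; the size is not.

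**The case against.** The case for leaving the rule alone has several parts.

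- **The fallback can beat the method it replaces.** This stands. With skewed data and low correlation, the rank sum test on follow-up values has more power than ordinary ANCOVA (85% against 75% at ρ = 0.3). It argues for keeping a rank method for skewed outcomes and against ANCOVA everywhere. It does not argue against a rank method that uses baseline.
- **The test might be run on change, so baseline is not discarded.** The text allows this reading. At high correlation little is then lost (96% against 98% at ρ = 0.75). At low correlation it is the weaker choice (63% against 88% at ρ = 0.3).
- **Covariates and response variables are commonly left to an analysis plan that is not shown.** True, and the unnamed covariate alone would be no finding. The switch itself and its unadjusted fallback are stated in the article.
- **The stakes are low.** Only secondary outcomes are involved, the rule is set in advance, the statisticians are to be blinded to allocation, and type I error holds. All of this stands and keeps the point modest.

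A reader might also infer that the skewed or bounded measures will nearly always go to the fallback. The documents give no distribution for any of them, so this is plausible but not established.

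**Conclusion.** The point holds as a modest one. The protocol fixes a residual-driven switch between two methods with different targets, and its fallback cannot adjust for a baseline that is collected. Under the assumed skewed data (gamma shape 2, 52 per arm, 0.5 SD shift, correlation 0.3 to 0.75), a baseline-adjusted rank test had more power than the rank sum test under either reading: by about 3 to 15 points on follow-up values and about 2 to 24 on change. The correlation, shape and effect are all assumptions.

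A stronger reading is tempting: that the switch always throws the baseline away and costs a fixed amount of power, up to some 26 points, against baseline-adjusted ANCOVA. The documents do not support it. They do not name the covariate or say that follow-up values are used. Under normal errors, losses of that size arise where the switch seldom triggers. Under non-normal errors, the comparison with ordinary ANCOVA changes sign with an unknown correlation. Nor is there any sign of inflated type I error. The primary analysis and the sample size are untouched.

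**What to change.** In the Statistical analysis section:

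1. Name the baseline value of the outcome as the ANCOVA covariate.
2. Fix one between-arm method for each secondary outcome before unblinding, the same at every visit, and remove the switch on residual normality.
3. For outcomes expected to be skewed, replace the rank sum test with baseline-adjusted rank ANCOVA (Quade).

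This takes a sentence or two and needs no new data. There are two costs. The rank method gives a test without an adjusted mean difference. If the data prove normal it also gives up a little power: 77/86/95% against 78–79/88–89/96–97% for ANCOVA at correlations 0.4/0.6/0.75, or about 1 to 3 points. Prescribing ANCOVA for every outcome, even with robust standard errors, is not the better remedy, because ordinary ANCOVA lost power to the rank methods under skewness at low correlation.

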**Discussion:**

This study will be the first randomized and controlled pilot trial of acupuncture on alleviating the symptoms of pSS with relatively long-term follow-up. The result of the study might offer a new option to treat pSS and might be a clinical proof that acupuncture has beneficial effects on pSS.

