#### Secondary outcome

Secondary outcomes include each items of NAS scores from week 0 to 8. These items will be measured individually at baseline, 3 times a week in week 1 to 8, once a week in week 12, 16, 20, 24. The secondary outcomes also include:EULAR Sjögren’s Syndrome Patient Reported Index (ESSPRI) [16] is a very simple index completed by patients to measure symptoms in pSS. With good construction validity, it is used as an outcome measure in clinical trials. There is a 0–10 numerical scale for each of the four domains, dryness, discomfort (including pain), global fatigue and mental fatigue, which are gathered to form the ESSPRI. For sicca features, six components were identified, which are ocular, oral, skin, nasal, tracheal and vaginal.EULAR Sjögren’s Syndrome Disease Activity Index (ESSDAI) [17, 18] is a clinical index completed by physicians to measure disease activity in patients with pSS. There are 12 organ-specific ‘domains’ contributing to disease activity. For each domain, features of disease activity are classified into three or four levels according to their severity.Schirmer test score and unstimulated salivary flow [19]: these two tests are the objective reflection to the lacrimal gland and salivary glands, the results of which can be greatly impacted by the operator. Thus, there will be a technician performing these two tests during the whole trial to maintain the homogeneity of the operation.Serum Immunoglobulin G, A, M levels [20]: Immunoglobulin G (IgG) is commonly believed in clinic a reflection of pSS symptom activities and a study shows weak associations between increasing fatigue and serum IgG, and the pro-inflammatory cytokine interleukin-17 (IL-17), were observed.Medical Outcome Study Short Form 36 Short-Form Health Survey (SF-36) [21, 22] is a self-administered questionnaire with 36 items, which assesses the concepts of physical function, role limitations due to physical problems, social function, body pain, general mental health, role limitations due to emotional problems, vitality, and general health perceptions. Note that both physical and mental component summaries can be combined. Scores range from 0 to 100, with higher scores indicating better health status [23].Salivary glands ultrasounds [24]: image of salivary glands structures. This can be quantified by a form based on different features.Hospital Anxiety and Depression (HAD) scale score [25]: A self-assessment scale which has been developed and found as a reliable instrument for detecting states of depression and anxiety in the setting of an hospital medical outpatient clinic.

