### Efforts to minimize some other bias

Besides the details of sham needles and the inform strategy, there are a lot of other efforts we take to minimize the possible bias. We will give subjects acupuncture in one room and interview them in another, so that the physicians, the interviewer, the data collectors, and the statistics will be blind to the group allocations. What else, to ensure the consistency of manipulation in repeated courses of real/sham acupuncture, we will train the acupuncturist and write a standard operation procedure (SOP) and this acupuncturist will stick to SOP throughout the whole study. It is designed to be based on a specialists’ consensus, which is 3 times of acupuncture a week in the first 4 weeks followed by twice a week in the second 4 weeks. It obeys the acting rules of this traditional therapy. And the subjects will be followed up by another 16 weeks besides 8 weeks of acupuncture, in order to ensure the relatively long-term effects to be observed rather than only the short-term ones.

When NAS scores are collected in CRF, a general pSS condition of the last 24 h will be asked to avoid temporary diverse interferences only existing during the interviews, such as mental relaxation in weekend, weather changing, and unexpected events in life, etc. Schirmer test, unstimulated salivary flow, and salivary grand ultrasound will be performed by the same technicians to maintain the consistency, before and after the 8-week intervention and during the follow-up, which also reduces bias.

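### One unadjusted P<0.05 rule covers the primary, at least 13 secondary measures and the within-arm tests, with nothing to separate confirmatory from exploratory results

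*Protocol article*

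**What the plan says.** The Primary outcome section of the protocol article fixes one primary contrast: the proportion in each arm with at least a 30% reduction in two or more of the three symptom scores, using the average over weeks 2 to 8. The Sample size section sizes the trial on that contrast alone, at two-sided 5% and 80% power.

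The Secondary outcome section lists the three NAS items (dryness, pain, fatigue), ESSPRI, ESSDAI, Schirmer test, unstimulated salivary flow, IgG, IgA, IgM, SF-36, salivary gland ultrasound and HAD. That is 13 measures if SF-36 and HAD each count once. The NAS items are "measured individually at baseline, 3 times a week in week 1 to 8, once a week in week 12, 16, 20, 24". The rest follow a common schedule: "For the secondary outcomes listed above, the measurements are conducted at baseline, in week 8, 16 and 24".

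The Statistical analysis section gives the between-arm method, "For secondary outcomes, the analysis of covariance (ANCOVA) will be used if the residual are normal distributed, otherwise Wilcoxon rank sum test will be applied", and also prescribes tests against baseline: "For comparison with the baseline, a repeated measures data analysis of variance (ANOVA) or Wilcoxon signed rank test will be used for continuous data". It closes with one threshold for everything: P "<0.05 with two-tailed test indicates statistical significance". The article attaches no order, key visit, link to the primary or exploratory label to any secondary.

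**The concern.** The primary ends at week 8 and concerns symptoms only. Two things the trial sets out to learn lie outside it. The 16 weeks of follow-up exist "in order to ensure the relatively long-term effects to be observed rather than only the short-term ones", and the Discussion counts salivary gland structure and function and disease activity as the objective evidence. Only secondary outcomes can speak to either.

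Under the printed rule, any of these outcomes that crosses 0.05 may be reported as statistically significant, whatever the primary shows. The more outcomes and visits are tested, the more likely it is that at least one crosses by chance. Tests against baseline add a second route. They do not compare acupuncture with sham, yet a result that is significant in one arm and not in the other is easily read as an effect of treatment.

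**Working it through.** **The plan's own figure.** The article states no family-wise error rate for the secondaries, so there is nothing to reproduce. The check asks what the stated per-test threshold implies.

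**Inputs from the article.** Two-sided 0.05 per test, hence 0.025 per test in the direction of benefit (Statistical analysis). Measures and visits are as listed above (Secondary outcome).

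**Assumptions.** The article does not give the number of tests or their correlation. Two counts bracket the first, with SF-36 counted once and HAD as two scores (the HAD split is assumed):

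- All follow-up visits: 3 NAS items x 5 times (weeks 8, 12, 16, 20, 24) + 11 other scores x 3 times (weeks 8, 16, 24) = 15 + 33 = 48 tests. The 24 separate NAS readings in weeks 1 to 8 are not counted.
- One visit: 3 + 11 = 14 tests.

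**Independent tests.** P(at least one) = 1 - (1 - a)^k.

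- Either direction: 1 - 0.95^48 = 0.915; 1 - 0.95^14 = 0.512.
- Favouring acupuncture: 1 - 0.975^48 = 0.703; 1 - 0.975^14 = 0.298.

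**Correlated tests.** Take null z-statistics with common pairwise correlation r, written Z = sqrt(r) U + sqrt(1 - r) E, with U shared by all tests and E separate for each. Then, with c = 1.96,

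- either direction: 1 - integral over u of phi(u) [Phi((c - sqrt(r) u)/sqrt(1 - r)) - Phi((-c - sqrt(r) u)/sqrt(1 - r))]^k du;
- favouring acupuncture: 1 - integral over u of phi(u) [Phi((c - sqrt(r) u)/sqrt(1 - r))]^k du.

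| r | 48 tests, either | 48 tests, favouring | 14 tests, either | 14 tests, favouring |
|---|---|---|---|---|
| 0 | 0.915 | 0.703 | 0.512 | 0.298 |
| 0.3 | 0.795 | 0.44 | 0.438 | 0.22 |
| 0.5 | 0.613 | 0.31 | 0.348 | 0.17 |
| 0.8 | 0.295 | 0.15 | 0.197 | 0.10 |

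**Block structure.** With the same 48 tests, correlation 0.8 between visits of one outcome and 0.5 between outcomes, simulation gives about 0.56 for any significant result, 0.37 for two or more, and 0.28 for at least one favouring acupuncture.

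**Expected count.** 48 x 0.05 = 2.4 nominally significant results, half of them (1.2) favouring acupuncture. Correlation does not change these averages.

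**Within-arm tests, as an illustration.** Suppose both arms improve equally by 0.25 SD of change (assumed) with 60 per arm, and let a paired t-test stand in for the named methods. Power per arm is 0.478, so P(significant under acupuncture and not under sham) = 0.478 x 0.522 = 0.25, although the arms do not differ.

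**The case against.** The strongest reply is that this is a journal article with no SAP shown, and the ordering of secondaries, key visits and multiplicity are commonly left to a SAP. That stands as far as the missing procedure goes: its absence alone is no finding. What remains is the rule that is printed. It says what P<0.05 indicates, without limiting this to the primary, and a SAP that restricted secondary claims would have to depart from it.

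Other parts of the reply stand in full. The primary is a single, separately specified test on which the trial is sized, and its error rate is untouched. The article nowhere says that a secondary can establish efficacy if the primary fails, nor that efficacy is read from one arm being significant against baseline and the other not. The abstract calls the study a pilot and says only that the result "might be a clinical proof that acupuncture has beneficial effects on pSS", about the study as a whole. That label is not attached to the secondaries, though, and the trial is powered as a conventional two-sided comparison.

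A reader might also infer three stronger points that the article does not support:

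- That every secondary is tested at every visit. The article says when outcomes are measured, not which visits enter the between-arm tests.
- That an ineffective acupuncture would more likely than not show a significant benefit. In the common-correlation calculation for 48 tests that holds at r = 0 (0.70) but not at 0.3 (0.44) or above. Correlation is to be expected, because visits repeat in the same patients and the NAS items overlap with ESSPRI. Figures above one half at r = 0.3 or 0.5 count results in either direction, including those favouring sham.
- That a promised 5% family-wise rate is broken. The article gives a per-test threshold and claims no family-wise rate.

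**Conclusion.** The point holds as one about the printed decision rule. It gives the primary, the secondaries and the within-arm tests the same standing, and the follow-up and gland-function aims depend wholly on the secondaries. The chance that an ineffective acupuncture produces at least one significant secondary in its favour is about 15% to 70% if all visits are tested and about 10% to 30% if one is, for correlations from 0.8 to 0. In either direction the ranges are about 30% to 92% and 20% to 51%. Even the lowest figures are about four times the per-test rate (0.10/0.025 in favour; 0.197/0.05 in either direction). The test counts and correlations are assumptions. The within-arm figure of one in four is only an illustration, since the 0.25 SD is not in the article. Because the primary is protected, this is a cheap and worthwhile improvement and does not threaten the main result.

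**What to change.** In the Statistical analysis section, replace the blanket threshold with three statements:

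1. Only the between-arm test of the weeks 2-8 responder outcome is confirmatory, at two-sided 5%.
2. All secondary outcomes and time points are exploratory, reported as between-arm differences with 95% confidence intervals and without claims of statistical significance. If the sponsor wants a secondary claim, it can name a short sequence of its own choosing in advance, tested only after a significant primary, each at two-sided 5% and stopping at the first failure.
3. Change from baseline within each arm is presented descriptively, without P values.

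This takes a few sentences. It needs no new patients or data and costs the primary no power. The price is that the sponsor gives up claims of significance for secondaries outside any named sequence.
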